**Safety Consideration**

Exercise has a negligible risk in healthy adults, although maximal exercise does carry an extremely small risk of inducing myocardial ischaemia (“heart attack”). This program is low-volume and submaximal. Exercise will be at a submaximal level at most points in the study, but there is the possibility that the subject group will suffer from acute muscle soreness. Participants will not be eligible for this study if they are unable to exercise and will be excluded if they (i) have undergone surgery for weight loss; (ii) have had a prior history of heart, lung, cancer, kidney, endocrine, or liver disease. The risks associated with participating in this study are very small. It is more likely that the participants will gain benefit from the study than not. It will also provide evidence of the benefits of this sort of program for home workers which is essential given the low numbers of people adhering to the strength exercise guidelines

**Follow-Up**

Follow-up (via email check-in) for adverse events will be conducted post-intervention with data collection at the end of week 5. Participants will be allowed to keep the bands if they complete the follow-up data collection and respond to weekly adherence emails.

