**Study Design**

| **Study Design** | This study will utilise Randomised Control Trail (RCT) design. Following completion of the baseline measurements participants will be randomised (stratified by sex) to either a waiting list control or exercise intervention group. The control group will be asked to maintain their habitual activity and will be offered the intervention at the end of the study. Those in the exercise intervention group will all take part in a home-based low volume resistance exercise intervention. All participants will be asked to maintain their normal dietary habits throughout the study. |
| --- | --- |
| **Participants and Recruitment** | Participants will be adults (16 year and older) working from home at least 3 days per week and not currently achieving government strength guidelines of 2 days per week. Participants will not be eligible for this study if they are unable to exercise and will be excluded if they have had prior history of heart, lung, cancer, kidney, endocrine, or liver disease. Participants must pass the physical activity readiness questionnaire (PAR-Q) to be eligible to join the study. Invites to participate in the study will be sent out by the research team through their existing social media channels (Twitter, Facebook) and existing workplace contacts. |
| **Sample Size** | The current study is a pilot RCT study and no formal sample size calculation has been carried out. The main component of the intended work is to collect preliminary data to inform the sample size calculations for a subsequent definitive trial. Sample size is therefore based on guidelines from Julious (2005) suggesting a minimum of 12 participants per group, with allowance for a 50% drop out per group, meaning 50 employees will be recruited (25 people per group). In order to get a gender balance, males’ participants will be capped at 25 and the recruitment strategy adapted to ask for women only.  Reference: Julious SA. Sample size of 12 per group rule of thumb for a pilot study. Pharm Stat. 2005;4(4):287-91. |

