**Methodology**

[figure not shown]

| **Overview** | Data will be collected through an online survey and physical function tests. For the function tests, participants will either be provided with a video instruction or attend a live, online session with a researcher to see how to preform and score the tests. They will be asked to score their own tests and either email these to the researchers or enter the details into the online survey. All measures will be collected at baseline and after the 4 weeks. Each test/measure are detailed further below. |
| --- | --- |
| **Online Survey** | The survey will include questions on demographics (age, gender, ethnics background, postcode, qualification, general health), Job (employment status, job title, annual income, working from home status, hours worked, physical activity at work), work related outcomes (health related quality of life - HRQL, stress - Perceived Stress Scale, productivity - HWQ, work performance - HPQ short, work engagement - UWES), physical activity (PA levels -GPAQ, days of strength training) and musculoskeletal conditions (Roland-Morris Disability Questionnaire, the Keele STarT Back Screening Tool). In the follow up survey, no demographic data will be collected and instead, open ended questions will be provided for employees to feedback on any improvements or changes to the intervention and protocol. |
| **Push-Up Test** | The test requires participants to complete the maximal amount of push-ups consecutively without rest. Participants will either start on their knees if female or in the standard down position for males. The test will stop when the participant fails to reach the appropriate technique on two consecutive attempts. |
| **30-Second Sit to Stand Test** | The participant is encouraged to complete as many full stands as possible within 30 seconds. As participants will be at home, a stable dining chair will be recommended for the test. The number of stands a person can complete in 30 seconds is counted as the score. |
| **Participation** | Exercise adherence will be measured through weekly check-ins by email asking the participants to report the actual dose achieved compared to the dose prescribed. |

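### Adverse events are solicited once, by email after the programme, while the weekly emails are described as asking only about dose, so events are likely to be under-counted

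*Protocol*

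**What the plan says.** The Follow-Up section of the protocol sets one enquiry about harms: "Follow-up (via email check-in) for adverse events will be conducted post-intervention". The same sentence places the data collection at the close of week 5.

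The Participation row of the Methodology section sets up contact during the four weeks, for a different purpose: "Exercise adherence will be measured through weekly check-ins by email asking the participants to report the actual dose achieved compared to the dose prescribed". Controls have no prescribed dose, so these emails read as going to the intervention arm. For everything else the Methodology overview states: "All measures will be collected at baseline and after the 4 weeks".

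The Safety Consideration section names an expected harm: "there is the possibility that the subject group will suffer from acute muscle soreness".

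The Follow-Up section also attaches a reward to replying: "Participants will be allowed to keep the bands if they complete the follow-up data collection and respond to weekly adherence emails".

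On expected loss the protocol gives two figures. The Sample Size row under Study Design allows for 50% dropout, with 25 per group. The Statistical Analysis row allows for 20% attrition, with 30 in total. These two statements contradict each other and need reconciling as a separate matter. Here they serve only as the range of loss that the protocol itself contemplates.

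**The concern.** The exercise is done at home from video instruction, and the number of sets rises in weeks 3 and 4. A short-lived event such as soreness in week 1 would first be asked about some four weeks later. One retrospective question cannot readily tie an event to a week, an exercise or a missed session. No reason for a missed or stopped session is described as being collected while the programme runs, and adherence is analysed only as a percentage of 12 sessions.

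The enquiry also depends on a reply at the point where loss is greatest. Someone who has stopped answering the weekly emails no longer qualifies to keep the bands, and so has less reason to answer the last one. The missing-data rule does not help: it carries the baseline survey answer forward, and no baseline answer exists for an event that happens during the intervention.

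At stake is what this pilot can tell the planners of the definitive trial about tolerability, and how soon the team learns of a difficulty.

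**Working it through.** **1. The protocol's own figures.** With 12 per arm needed and loss d, the number to recruit per arm is 12/(1 − d).
- d = 0.50: 12/0.50 = 24 per arm, 48 in total. The protocol states 50, which is 25 per arm after rounding up.
- d = 0.20: 12/0.80 = 15 per arm, 30 in total. The protocol states 30.

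Both allowances reproduce. The planned loss per arm is 0.20 × 15 = 3 people, or 0.50 × 25 = 12.5, about 12 people.

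**2. What non-response does to the event rate.** The documents give no event rate and no response rate by event status, so the following are assumptions:
- p, the true share of participants with an event: 20% (10% and 30% also tried);
- d, the overall non-response to the enquiry: 20% or 50%, taking the protocol's dropout allowances as a stand-in;
- r, the ratio of non-response in people with an event to that in people without: 0.5 to 2.

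Formulas:
- non-response without an event: q = d / (p·r + 1 − p)
- non-response with an event: qA = r·q
- rate among responders: p(1 − qA) / (1 − d)
- count over all randomised, with non-responders taken as event-free: p(1 − qA)

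Example with p = 0.20, d = 0.50, r = 2: q = 0.50/(0.40 + 0.80) = 0.417 and qA = 0.833. The rate among responders is 0.20 × 0.167/0.50 = 6.7%, and the count over all randomised is 0.20 × 0.167 = 3.3%.

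Results for p = 20%:

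| r | d = 20%: responders | d = 20%: all randomised | d = 50%: responders | d = 50%: all randomised |
|---|---|---|---|---|
| 0.5 | 22.2% | 17.8% | 28.9% | 14.4% |
| 1 | 20.0% | 16.0% | 20.0% | 10.0% |
| 1.5 | 18.2% | 14.5% | 12.7% | 6.4% |
| 2 | 16.7% | 13.3% | 6.7% | 3.3% |

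True rates of 10% and 30% give the same pattern. At d = 50%, for r from 0.5 to 2, the rate among responders runs from 14.7% down to 1.8% for p = 10%, and from 42.4% down to 13.8% for p = 30%.

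**3. Reading the table.** The count over all randomised is below the truth in every row. The rate among responders is below the truth only where r exceeds 1, correct where r = 1, and too high where r is below 1.

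**4. Precision, a separate matter.** With no events in n responders, the one-sided 95% upper bound is 1 − 0.05^(1/n): 22.1% for n = 12, 18.1% for n = 15 and 11.3% for n = 25. Fewer replies widen the bound, but this says nothing about the direction of a bias.

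**The case against.** A reader might infer that people who stop through soreness or injury are the least likely to be counted, so that the trial's safety result is biased downwards. The documents do not support that as a fact. They give no data on who replies, and the rate among responders is low only if r exceeds 1, which is plausible but assumed. The protocol names no safety outcome, so there is no defined safety result to be biased.

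A reader might also infer that 3 to 12 intervention participants would never be asked. The Follow-Up section does not limit its email to completers. Stopping exercise, not replying and not being asked are three different things, and the most one can say is that some may never answer. Nor does setting 22.1% against 11.3% measure the problem. It shows imprecision, and it compares 50% loss with full response from all 25. Under the 20% allowance the contrast is 22.1% against 18.1%.

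Other information does reach the team. The second week's band depends on repetitions and perceived effort for each exercise, so some exercise-level feedback arrives during the programme. Weekly dose replies show missed sessions. The follow-up survey has back-disability measures and open questions. These points stand, and it would be wrong to say that all information on tolerability is lost. None of them asks about harms or reasons for stopping during the programme, however, and the survey depends on the same late reply.

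The programme is short, low in volume and submaximal, in screened adults, and no stated objective or analysis depends on the event count. That limits the weight of the point. The consent and information pages were not available; they may hold a route for spontaneous reports, which would supplement a systematic enquiry but not replace it.

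**Conclusion.** The point holds in a limited form. One enquiry after the programme, with 20% to 50% planned loss and short-lived expected events, makes under-counting likely and may leave the team unaware of a problem until the exercise period is over. The size of any bias is unknown. If non-responders are treated as event-free, the count over all randomised is low: at an assumed true rate of 20% it shows 13.3% to 17.8% with 20% non-response, and 3.3% to 14.4% with 50%. The rate among responders may be low, correct or high, depending on who replies. These figures rest on the assumed event rate and response ratios, and on non-response matching the dropout allowances.

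The planned comparisons of physical function and work outcomes are not affected. This is an inexpensive improvement to harm ascertainment. It belongs in the protocol, because no later analysis can recover events that were not asked about.

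**What to change.** - Add one item to the existing weekly adherence email: any pain, injury or new symptom that week, and whether it caused a missed or stopped session.
- State that the week-5 enquiry goes to everyone randomised, including those who stopped exercising.
- Report the number answering at each contact as the denominator for that contact, and show non-responders as unknown. Do not count everyone with at least one reply as fully observed: a person who replies in week 1 and then stops would pass as event-free.
- Base any between-arm comparison on the week-5 enquiry, which is the same in both arms, and report the weekly intervention-arm data descriptively. If the same weekly item is also sent to controls, the weekly data can be compared as well.

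The cost is one extra question a week in an email already planned, and slightly more reporting. Emailing controls weekly would add contact in a waiting-list arm whose outcomes are self-reported. Whether equal ascertainment is worth that is a matter of judgement, and the fix does not depend on it. The weekly item also relies on email replies, so it reduces the gap without closing it.

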**Data Management and Statistical Analysis**

| **Data Management** | Data will be collected from of an online survey and functional fitness tests. Both qualitative and quantitative data will be produced from the online survey which will be exported in the form of an Excel spreadsheet. Quantitative data will be transferred from the Excel spreadsheet and analysed in the data analysis package SPSS. Qualitative data from the survey will be exported into NVivo. Fitness test data produces a score which will either be recorded by the researcher for live, online fitness test, or entered into the survey for those completing the tests in their own time.  Only the named investigators will have full access to the data obtained. The information obtained will be anonymised and identifiable data will not be passed on to anyone outside the named investigators. Data will be stored on personal or University of Glasgow computers of the named investigators on the University server. Access will be restricted by password-protection and data will be stored for 10 years. Data will be backed up through the University of Glasgow OneDrive cloud. |
| --- | --- |
| **Statistical Analysis** | Survey data will be exported to Excel (2016), and all statistical analysis will be performed using SPSS version 28.0 software (SPSS Inc., Chicago, IL). A sample size of 30 was determined based on guidelines for feasibility studies by Julious (2005) suggesting a minimum of 12 participants per arm, and allowing for a rate of 20% attrition. No further formal sample size calculations were undertaken due to this being a feasibility study.  Data will be visualised using box plots to check for outliers and then checked for normal distribution. Any missing data will be imputed using the corresponding answer given in their baseline survey answer (last-observation-carried-forward). Demographic data that will be gathered at baseline will be cleaned to condense the number of categories where necessary, so that no category had fewer than 5 people in it. Continuous variables will be presented as mean ± SD, and categorical variables as n (%). A 2x2 mixed ANOVA will be conducted to examine the group x time interaction effects on physical function tests and work-related outcomes. All analyses will be treated as intention-to-treat. Assumptions will be checked for all statistical analyses, and significance will be set at p<0.05. Adherence will be calculated as the percentage of self-reported sessions completed compared to those expected (12 expected sessions). |

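### The 2x2 mixed ANOVA is a t-test on change that leaves out sex, the stratification factor; ANCOVA on baseline and sex would usually be modestly more precise

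*Protocol*

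**What the plan says.** The Statistical Analysis section names one model for all the function and work outcomes: "A 2x2 mixed ANOVA will be conducted to examine the group x time interaction effects on physical function tests and work-related outcomes". It names no covariate and no sex term, and "significance will be set at p<0.05". Missing follow-up values are to be replaced by the participant's baseline value, continuous variables are to be summarised by mean and SD, and the analysis is described as intention-to-treat.

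Three other statements bear on this model:

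- Methodology, Overview: "All measures will be collected at baseline and after the 4 weeks", so there are exactly two time points.
- Study Design: "participants will be randomised (stratified by sex) to either a waiting list control or exercise intervention group", so there are two arms and sex is a design factor.
- Methodology, Push-Up Test: "Participants will either start on their knees if female or in the standard down position for males". The Project Summary lists the push-up test as a primary outcome.

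The Sample Size section adds that the main purpose is to gather preliminary data for sizing a definitive trial. Baseline-adjusted or sex-adjusted analysis is mentioned nowhere in the protocol.

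**The concern.** A two-by-two mixed ANOVA looks like a model of the whole data set, but its interaction test uses only each person's change. It subtracts baseline with a fixed slope of 1, whatever the data say the slope is. In a randomised trial this usually costs precision compared with letting the data estimate the slope, and the cost matters most in a trial this small. The model also ignores sex, although the design balances the arms on it, so any sex difference in change stays in the error term.

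A second issue follows from the trial's purpose. The push-up scores of women and men come from different versions of the test. If a single SD is computed over everyone, it contains the gap between versions as well as the variation between people, and the definitive trial could be sized on it.

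**Working it through.** **Inputs.** From the protocol: two arms, two times, stratification by sex, significance level 0.05 (taken as two-sided), at least 12 per arm. Not in the protocol and therefore assumed: SD 1 at both times, rho from 0.3 to 0.95, a true effect of 0.5 SD for power, and equal numbers of men and women.

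**The plan's own figures.** The Statistical Analysis section says "A sample size of 30 was determined based on guidelines for feasibility studies by Julious (2005) suggesting a minimum of 12 participants per arm", "allowing for a rate of 20% attrition": 24 / (1 − 0.20) = 30, which reproduces. The Sample Size section reaches 50 from a 50% dropout: 12 / (1 − 0.50) = 24 per group, or 48, against a stated 50 (25 per group). The two totals disagree, which is a separate matter; here they only set the range of 12 to 25 per arm.

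**Step 1: what the planned test is.** In one simulated data set, the interaction F was 0.22254 and the squared t on change was 0.22254. They are the same test.

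**Step 2: precision.** Per arm and up to a common factor, the variance is 2(1 − rho) for the change score and 1 − rho² for ANCOVA. The ratio is (1 + rho)/2. For a small trial of N people in total, estimating the baseline slope multiplies the ANCOVA variance by about 1 + 1/(N − 4), and the residual degrees of freedom fall from N − 2 to N − 4 with baseline and sex in the model:

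CI width ratio = √[(1 + rho)/2 × (1 + 1/(N − 4))] × t(N − 4)/t(N − 2).

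At 12 per arm (N = 24) and rho 0.5: √(0.75 × 1.05) × 2.0860/2.0739 = 0.893.

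| rho | Variance ratio | CI width ratio, 12 per arm | CI width ratio, 25 per arm | Power at 12 per arm, change → ANCOVA |
|---|---|---|---|---|
| 0.3 | 0.650 | 0.831 | 0.816 | 0.168 → 0.222 |
| 0.5 | 0.750 | 0.893 | 0.876 | 0.216 → 0.260 |
| 0.7 | 0.850 | 0.950 | 0.933 | 0.327 → 0.357 |
| 0.8 | 0.900 | 0.978 | 0.960 | 0.457 → 0.475 |
| 0.9 | 0.950 | 1.005 | 0.986 | 0.745 → 0.742 |
| 0.95 | 0.975 | 1.018 | 0.999 | 0.959 → 0.953 |

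**Step 3: baseline carried forward.** If a share m of follow-up values is replaced by baseline (dropout at random assumed), the observed correlation is about m + (1 − m) × rho. With 25 per arm, m = 0.5 and rho 0.5, it becomes 0.5 + 0.5 × 0.5 = 0.75. The CI width ratio is then √(0.875 × 1.0217) × 1.0011 = 0.947, so the gain drops from about 12% to about 5%. A true rho of 0.8 becomes 0.9, and the gain is about 1%.

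**Step 4: chance imbalance.** Given a baseline difference d between arms, the change-score estimate is off by (1 − rho)d in the opposite direction, because it subtracts all of d where only rho × d should go. The SD of d is √(2/n): 0.41 at 12 per arm and 0.28 at 25. At rho 0.5 and 12 per arm, a typical imbalance therefore moves the estimate by about 0.5 × 0.41 = 0.20 SD. Averaged over randomisations this is zero.

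**Step 5: leaving out sex.** Simulation at 12 per arm, balanced by sex within arm, 3,000 runs per setting:

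- A constant sex gap of 1 SD at both times cancels in the change score. At rho 0.5, power is 0.207 and type I error 0.046, both with and without the gap.
- If change also differs by 0.5 SD between the sexes (assumed), type I error of the planned test falls to 0.041, 0.036 and 0.024 at rho 0.5, 0.7 and 0.9. Its power is 0.187, 0.272 and 0.634, against 0.255, 0.348 and 0.748 for ANCOVA with baseline and sex.
- In the same setting, ANCOVA with baseline but without sex has power 0.186, 0.272 and 0.613, so the sex term is needed as well as the baseline.

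**Step 6: pooled push-up SD.** With a 50/50 sex split and a gap of g within-sex SDs between the versions, the pooled SD is √(1 + 0.25g²) times the within-sex SD: 1.03 at g = 0.5, 1.12 at 1 and 1.25 at 1.5. Required sample size goes with the square: 6%, 25% and 56% larger if this SD were used. The pooled correlation rises too: a within-sex rho of 0.5 becomes (0.5 + 0.25)/(1 + 0.25) = 0.60 at g = 1.

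**The case against.** The strongest reply is that nothing here is an error. The change-score test is unbiased under randomisation and keeps its significance level. The trial is a pilot without formal powering, and the choice between two valid analyses is one of efficiency. All of that stands.

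A reader might go further than the protocol supports in four ways:

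- *That adjustment is a free gain, worth 10% to 25% of the variance.* That range comes from the large-sample ratio at rho 0.5 to 0.8. No rho is given, the small-sample cost removes the gain at about 0.9 in a trial of 12 per arm, and the planned imputation pushes the observed rho upwards.
- *That the standard error is wrong because the stratifier is omitted.* This is so only if change differs by sex, which two test versions make plausible but the protocol does not show. Even then the planned test errs on the conservative side.
- *That mixing knee and standard push-ups spoils the test.* Each person does the same version twice, so a fixed gap drops out of the change. Nor does a sex term put the two versions on one scale: the adjusted effect still averages over both.
- *That the baseline slope should also differ by sex for push-ups.* In a simulation at 12 per arm (common true slope, equal change by sex), this widened the interval relative to the change score by 0.5% at rho 0.8 and 3.5% at 0.9. It is not worth its cost.

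It can also be said that the protocol never states that a sex-pooled raw push-up SD will be used for the definitive trial. That is fair, and a fixed gap would also drop out of a change SD or a sex-adjusted residual SD. The SD inflation is therefore a conditional risk. Finally, the analysis model cannot be treated as something left to a statistical analysis plan, because the protocol itself fixes it.

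**Conclusion.** The point holds as a matter of efficiency and reporting. The planned analysis is valid, but it is a t-test on change that fixes the baseline slope at 1 and omits the stratification factor. At 12 per arm, ANCOVA on baseline and sex gives a confidence interval about 11% narrower at rho 0.5, 5% at 0.7 and 2% at 0.8, and one unchanged or up to 2% wider at 0.9 to 0.95. These figures assume normal outcomes, equal SDs at both times, no sex difference in change and no carried-forward values. Carrying baseline forward reduces the gain, to about 5% at a true rho of 0.5 with 25 per arm and half the values carried forward. A sex difference in change increases it. The 3% to 25% inflation of a pooled push-up SD applies only under an assumed gap of 0.5 to 1.5 within-sex SDs and an even sex split, and matters only if that SD is used for planning. The change is worth making because it is cheap, not because the planned test would mislead.

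**What to change.** In the Statistical Analysis section, replace the mixed ANOVA by this: for each continuous outcome, regress the follow-up score on group, baseline score and sex, and report the adjusted group difference with its 95% confidence interval. For push-ups, also report baseline and follow-up means and SDs separately for women and men, and take the SD for the definitive trial from within sex or from the adjusted residuals.

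The cost is a sentence or two of text and two residual degrees of freedom (22 to 20 at 12 per arm). No additional data are needed: baseline scores and sex are already collected. If rho proves to be 0.9 or higher in a trial of 12 per arm, the interval may be up to 2% wider than under the planned analysis. Reporting the observed correlation for each outcome would cost nothing and would help in planning the definitive trial.

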**Expected Outcomes of The Study**

This study will generate evidence on the effectiveness of a low-cost, home-based resistance training intervention for improving workplace outcomes and strength. Insights may inform workplace wellness policies and health system strategies by promoting scalable, preventative approaches to physical function and well-being.

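### A pilot with no power calculation tests five to seven outcomes at unadjusted p<0.05, without an exploratory label, and expects evidence of effectiveness

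*Protocol*

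**What the plan says.** The title calls the study a pilot feasibility trial. The Sample Size row of Study Design states: "The current study is a pilot RCT study and no formal sample size calculation has been carried out". The same row gives the main component of the work as preliminary data for sizing a later definitive trial. The Statistical Analysis row agrees on the reason: "No further formal sample size calculations were undertaken due to this being a feasibility study".

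The analysis is confirmatory in form: "A 2x2 mixed ANOVA will be conducted to examine the group x time interaction effects on physical function tests and work-related outcomes", and "significance will be set at p<0.05". The section does not adjust for multiple outcomes and does not call the tests exploratory.

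The Project Summary names two primary outcomes (sit-to-stand and push-up) and three secondary ones (stress, engagement, productivity), five in all. The Online Survey row of Methodology lists five work-related outcomes, adding health-related quality of life and work performance. With the two function tests that makes seven.

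Expected Outcomes of The Study says: "This study will generate evidence on the effectiveness of a low-cost, home-based resistance training intervention". The Project Summary expects the same.

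The Participation row of Methodology collects adherence by weekly email, "asking the participants to report the actual dose achieved compared to the dose prescribed". The analysis summarises it more coarsely: "Adherence will be calculated as the percentage of self-reported sessions completed compared to those expected (12 expected sessions". Neither adherence nor any other feasibility measure is named as an outcome.

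**The concern.** The protocol uses feasibility status to set aside power, then plans significance tests and an effectiveness conclusion of the kind that power and error control exist to protect. Two results would be hard to interpret. One significant result among several unadjusted tests could be chance, yet it would fit the expected conclusion and could pass into the employer resources described under dissemination. A non-significant result would be compatible with a moderate benefit.

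The quantities that a pilot is run to obtain have less prominence than the tests. Retention, the precision of the SD and the baseline-to-follow-up correlation are not listed as outputs. Adherence is cut to a session count although fuller dose information is requested.

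**Working it through.** **1. The plan's own sample sizes.** Both start from a minimum of 12 per arm.
- Statistical Analysis, 20% attrition: 12 / (1 - 0.20) = 15 per arm, 30 in total. This reproduces the stated 30 exactly.
- Study Design, 50% dropout: 12 / (1 - 0.50) = 24 per arm, 48 in total, against 50 stated (25 per arm).

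Neither figure comes from a significance level, power or effect size. The two conflict and need reconciling as a separate matter. Here 12, 15 and 25 per arm are all carried forward.

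**2. Chance of at least one false positive.** With k independent tests at 0.05 and no true effects, this is 1 - 0.95^k.
- Two primaries: 1 - 0.95^2 = 9.8%.
- Five outcomes (Project Summary): 1 - 0.95^5 = 22.6%.
- Seven outcomes (Online Survey list plus function tests): 1 - 0.95^7 = 30.2%.

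The outcomes are probably correlated, which lowers these figures. Simulating seven equally correlated normal test statistics (400,000 draws) gives about 27%, 23% and 18% at correlations of 0.3, 0.5 and 0.7.

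**3. Power of the planned test.** In a 2x2 mixed ANOVA the interaction test is equivalent to a two-sided t test on change. If rho is the baseline-to-follow-up correlation:
- SD of change = SD x sqrt(2(1 - rho)), which is 1.00 SD at rho = 0.5 and 0.632 SD at rho = 0.8.
- Noncentrality = (difference / SD of change) x sqrt(n/2), with 2n - 2 degrees of freedom.

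The protocol gives no effect size or correlation. The values below are assumptions: differences of 0.5 and 0.8 baseline SD, rho from 0.5 to 0.8. For 0.5 SD at 12 per arm the noncentrality is 0.5 x 2.449 = 1.22 at rho = 0.5, and (0.5 / 0.632) x 2.449 = 1.94 at rho = 0.8.

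| Analysed per arm | Power, 0.5 SD | Power, 0.8 SD | Difference detectable with 80% power |
| --- | --- | --- | --- |
| 12 | 22-46% | 47-84% | 1.20-0.76 SD |
| 15 | 26-55% | 56-92% | 1.06-0.67 SD |
| 25 | 41-78% | 79-99% | 0.81-0.51 SD |

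In each cell the first figure is for rho = 0.5 and the second for rho = 0.8. The table assumes complete data on the number shown; it does not model the planned carrying forward of baseline values.

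**4. What the adherence summary loses.** The Intervention and Development row gives eight exercises, three sessions a week, two sets in weeks 1-2 and three in weeks 3-4.
- Prescribed sets: 6 x 8 x 2 + 6 x 8 x 3 = 96 + 144 = 240.
- All 12 sessions done, but always at two sets: sessions 12/12 = 100%; sets 12 x 8 x 2 / 240 = 192/240 = 80%.
- Stopping after week 2: sessions 6/12 = 50%; sets 96/240 = 40%.

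The 240 is illustrative, because the same row allows the steering group to switch exercises or reduce reps and sets.

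**The case against.** The strongest reply is that the pilot's purpose is better served than it first appears. Continuous variables are to be presented as mean and SD, and the SD is the main input to a sample size calculation. Physical function is a sensible primary variable if its SD is what the next trial needs. Open-ended follow-up questions on the intervention and protocol are planned, with qualitative data going to NVivo. All of this stands. A reader might infer that feasibility is not measured at all, or that the definitive trial gets nothing from this one. The document does not support either inference. What is true is narrower: no feasibility measure is a designated outcome, and retention, correlation and precision are not listed.

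A reader might also infer that the trial is unable to detect any effect. That goes too far. At an assumed 0.8 SD and correlation 0.8, power is 84% with 12 per arm and 99% with 25. Likewise 30% is the independence figure for seven outcomes and should not be quoted alone.

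The policy language is hedged: insights may inform workplace policy. Nothing in the text says that a non-significant result will be reported as no effect. Making feasibility measures primary is one convention, and this document does not oblige it. Nor is a log of people approached described, so a recruitment rate cannot be assumed available.

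Finally, a separate analysis plan might label the tests exploratory. It would not fully answer the point, because the significance rule, the adherence formula and the effectiveness wording are fixed in this protocol.

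**Conclusion.** The point holds as a mismatch between purpose, analysis and expected conclusion. The design supports estimation for planning. It does not support a conclusion on effectiveness drawn from several unadjusted tests with no stated power. The false-positive range depends on the number of outcomes counted and their correlation: up to 9.8% for the two primaries, and about 18-30% for all seven. The power range depends on the assumed effect and correlation, and at 12 or 15 per arm it stays near or below one half for 0.5 SD. The adherence point is secondary: a session count is a legitimate measure, but alone it cannot show whether the increase to three sets was achieved. This should be changed. It alters what the trial may conclude, while the comparisons themselves remain worth reporting.

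**What to change.** - **Statistical Analysis:** replace the p<0.05 decision rule with between-group differences and 95% confidence intervals, labelled exploratory.
- **Project Summary and Expected Outcomes of The Study:** replace the effectiveness wording with preliminary estimates to inform a definitive trial.
- **Planned outputs:** list retention and outcome completeness, each with a 95% confidence interval; for each function test, the SD with its confidence interval and the baseline-to-follow-up correlation; and dose adherence, as sets done over sets prescribed in the final intervention, beside sessions out of 12.

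Physical function may remain the primary outcome. These outputs draw on data the protocol already plans to collect, provided that the weekly check-in is worded so that sets can be counted. The cost is a more modest claim and slightly more tabulation.
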